## Abstract

**Background:**

Underserved ethnic minority populations experience significant disparities in HIV, hepatitis C virus (HCV), colorectal cancer (CRC), and cervical cancer incidence and mortality. Much of the excess burden of these diseases among underserved communities is due to lack of preventive care, including screening. Barriers to disease screening include low awareness, lack of access to care and health insurance, and cultural beliefs regarding disease prevention. Our current trial aims to examine community health worker (CHW)-delivered, home-based multi-modality screening for HIV, HCV, CRC, and cervical cancer simultaneously.

**Design:**

We are conducting a randomized pragmatic trial among 900 Haitian, Hispanic, and African-American participants from diverse underserved communities in South Florida. People between the ages of 50 and 65 who have not had appropriate HIV, HCV, CRC, and cervical cancer screening per United States Preventive Services Task Force (USPSTF) recommendations are eligible for the study. Participants are recruited by CHWs and complete a structured interview to assess multilevel determinants of disease risk. Participants are then randomized to receive HIV, HCV, CRC, and cervical cancer screening via navigation to care by a CHW (Group 1) or via CHW-delivered home-based screening (Group 2). The primary outcome is completion of screening for each of these diseases within 6 months post-enrollment.

**Discussion:**

Our trial is among the first to examine the effectiveness of a CHW-delivered, multimodality, home-based disease-screening approach. If found to be effective, this approach may represent a cost-effective strategy for disease screening within underserved and underscreened minority groups.

**Trial registration:**

Clinical Trials.gov # NCT02970136, registered November 21, 2016.

## Background and rationale

Minority, low income, and underinsured communities are at excess risk of morbidity and mortality from HIV, hepatitis C virus (HCV), colorectal cancer (CRC), and cervical cancer [1–10]. Lack of screening and/or early detection contributes greatly to this excess risk. Barriers to appropriate screening include poverty, language difficulties, limited access to health care (including, but not limited to, lack of health insurance), low health literacy, lack of knowledge about various diseases and the importance of early detection, disease fatalism or the belief that disease implies death, and cultural norms about health and disease prevention. Alongside these barriers, historically and currently these communities have also been subject to discrimination and anti-immigrant policies, which further complicates the issue of accessing routine screening. 

Alternative screening strategies, such as screening via home-based and point of care tests, may address some of these barriers. Home-based tests for HIV, HCV, CRC, and cervical cancer are currently available, but not yet widely used.^i-iv^ With these, individuals can test themselves outside a formal clinical setting. Both within and outside the USA, randomized studies of home-based disease screening (most using mailed kits) have shown increased rates of screening [11, 12]. These screenings are most effective when delivered by a community health worker (CHW) who is knowledgeable regarding community values and norms [12].

We have recently completed two randomized trials of CHW-delivered, home-based cervical cancer screening among Haitian, Hispanic, and African American women living in South Florida [13, 14]. These studies revealed that CHW-delivered, home-based screening was superior in increasing cervical cancer screening uptake. We now seek to examine whether additional home-based screening modalities can be delivered together to improve not only cervical cancer screening but also screening for HIV, HCV, and CRC among racial/ethnic minorities.

### Aims and objectives

Our specific aim is to determine if a strategy in which CHWs deliver multimodality, home-based screenings results in an increase in the proportion of participants screened for all four conditions (HIV, HCV, CRC, and cervical cancer) as compared to a strategy in which patients are navigated to primary care by a CHW at one of our participating health centers. Our study will have over 95% power to examine our primary hypothesis that the CHW led multimodality screening strategy will result in a 15 percentage point increase in participants who are up to date in screening for these four conditions (three for men) as compared to a strategy of linkage to primary care. Secondary analysis will examine increases in screening for each of the four conditions individually. Subgroup analysis will include examining outcomes by race/ethnicity and by gender.

## Methods

### Trial design/setting

We are recruiting 900 participants from various underserved communities in Miami-Dade County. Of the 2.8 million county residents, 69% are Hispanic and 18% are Black [15]. Further, whereas 30 years ago, Cubans made up 80% of Miami Hispanics, over the last decades a rapid influx of immigrants from most of Latin America now make Miami as the most diverse Latino community in the USA. In 2018, 52%Latinos were Cuban, 20%^17^ were South American, 15% were Central American, and 9% were Puerto Rican or Dominican[15]. South Florida’s Black population is also diverse, and Miami has the largest population of Black immigrants. Nationally, the Black immigrant population has quadrupled and they will represent nearly 20% of Black Americans in 50 years. However, at present, more than a third of Black residents in Miami are foreign-born. This includes the 484,000 Haitians living in Florida, who represent 47% of all US Haitians [16]. For the current study, we are focusing recruitment primarily in three communities: Little Haiti (predominantly Haitian), Hialeah (predominantly Hispanic), and South-Dade (racially/ethnically mixed).

#### Conceptual approach

Our conceptual approach to addressing disparities in cancer control is informed by Social Ecological theory, which emphasizes the importance of, and interaction between, larger systemic factors (relationships, communities, culture, etc.) and individual factors in determining health behavior [17]. Thus our approach aims to address the aforementioned barriers to cancer screening not only on the individual level, but also on the larger systemic, cultural, and community levels. To successfully address cancer control from a socioecological perspective, our study utilized a community-based participatory research (CBPR) approach. CBPR addresses cancer control at multiple levels of influence via the engagement of key community stakeholders [9]. These stakeholders advise and inform the development of interventions tailored specifically to meet unique community need, which facilitates the implementation at both the individual and community levels. Our community partners, including federally qualified health centers (FQHCs), community-based organizations, community leaders, as well as members of the target communities, provide critical input regarding all aspects of study design and implementation within the current study.

### CHW training

As with prior studies, our community outreach, recruitment, and intervention approaches are led by CHWs. Our study team includes three CHWs all from our target communities who are bilingual in either English and Spanish or English and Haitian Creole. All three are certified CHWs by the Florida Certification Bureau and each has over 5 years of experience as a CHW. All three have completed the University of Miami’s required research training in human subject research as well as formal CHW research training using modules developed by our study team. They also received additional study-specific training from our academic research team, organized into three modules: (1) health education on each of the four conditions, (2) specimen collection procedures, and (3) study data collection procedures. Each of these sessions was interactive and hands-on, and CHWs were able to practice and receive feedback on their data collection and study procedure skills.

### Eligibility

#### Inclusion criteria

To be eligible individuals must be: (a) Haitian, Hispanic, or Black, (b) report not having had appropriate screening for at least one of the following HIV, HCV, CRC, and cervical cancer (as per 2017 United States Preventive Services Task Force (USPSTF) guidelines: never had a HIV test; never had a HCV test; not had a colonoscopy in last 10 years and/or stool-based test in the last year; and not had a Pap smear within the past 3 years), and (c) age 50–65 years. Each preventive test has different age and other eligibility criteria. For example, cervical cancer screening is recommended for women ages 21–65, CRC is recommended from ages 50–75, and HCV is recommended for persons born between the years of 1945 and 1965. After consultation with our community partners, we selected this simplified age criterion (50–65 years), which maximizes the number of tests for which participants would be potentially eligible (three for men, four for women).

#### Exclusion criteria

Individuals are not included in the study if they: (1) plan to move out of the county during the next 6 months, (2) have current or prior enrollment (5 years) in any research study that involved screening for these conditions, (3) are unable to consent, and/or (4) are currently pregnant.

### Recruitment

Trial recruitment occurs via convenience sampling at community-based locations such as markets, churches, botanicas, and health clinics, as well as via the social networks of our CHWs and community partners. The CHWs approach potentially eligible individuals, screen for eligibility, and explain the study. Eligible and interested individuals are asked to provide their contact information, and CHWs will try up to ten times to contact eligible individuals to schedule them for informed consent and study intake. Participants who agree to participate complete a 30‑minute intake interview in their home or location of their preference. The CHWs work closely with our two bilingual research associates (RAs) to set up these visits during which informed consent and study intake occur. Our RAs are master’s level highly trained research professionals. Upon completion of the intake interview, participants are randomized into one of two interventions.

### Allocation of trial interventions

Following the study intake, participants are randomized to one of the two study interventions by the study biostatistician, using REDCap’s randomization module. The module randomizes study participants electronically, and randomizes within study sites to account for nesting. The CHWs are notified via email of the assignment of participants following the randomization, and will follow up with participants within a week to inform them of their assignment, and to schedule a home visit (if the participant is in the home-based testing arm). Notably, while participants and CHWs are aware of group assignment, the community health educator (CHE), who collects study outcome data, is blinded to participant assignment.

#### Intervention Group 1—CHW-delivered navigation to primary care (PC) for disease screening

For participants assigned to Group 1, CHWs work closely with their FQHC supervisor to develop tailored navigation approaches appropriate for each person (consistent with the pragmatic trial design). First, they contact participants to assess which preventive services they are eligible for using a checklist based on the above criteria. For participants who already have a primary care provider (PCP), CHWs encourage such persons to follow up with their provider for needed tests. If they do not have a PCP or prefer not to go to their PCP for such testing, the preferred approach is to navigate participants to primary care services at local FQHCs where providers as part of routine care evaluate patients for needed preventive services. CHWs emphasize that while they are following a broad set of screening guidelines, only a PCP will know which preventive services are needed for each person based on their unique circumstance and risk profiles. As health center outreach workers, CHWs do not limit the scope of work to the four screening services. They also help link study subjects with other services offered by the centers (e.g. facilitated enrollment in health insurance plans, immigrant and refugee programs, behavioral health, and programs for people with diabetes), as needed. Participants may also prefer to obtain these services from other locations such as Project Screen (free cervical cancer screening for women age > 50), locations providing anonymous HIV and HCV testing, or health fairs sponsored by health centers or the University of Miami. In the third year of the study, the University of Miami began a separate, community-based cancer screening program using a mobile van that offers these screening services for free. On average, the vehicle goes to each of these communities at least once a month. Thus, we included the mobile van as an additional screening referral option for study participants in this group.

#### Intervention Group 2—CHW-delivered, home-based testing (HBT)

The CHWs develop tailored approaches appropriate for each participant in Group 2. First, CHWs use a checklist (as described above) to help determine which screening tests are needed. Participants in Group 2 are offered home-based testing. For these participants, there are various strategies CHWs may use. First, the CHW and the participant select a place of mutual agreement to conduct the needed screenings. Most typically, it will be at the participant’s home, although it can be at another community location. At the intervention visit the CHWs perform HCV and HIV screenings and provide post-test counselling. For the cervical cancer screening, they instruct participants how to do human papilloma virus (HPV) self-sampling. Participants are offered HPV self-sampling at the intervention visit, and typically provide the self-collected specimen to the CHW during the intervention visit. If for some reason the participant cannot complete the HPV self-sampling during the intervention visit, the CHWs will leave the kit with the participant and the participant can send the sample via mail. Persons needing a fecal immunochemical test (FIT) receive instruction on how to do the test and are given the kits, which they mail back. For mailed kits, the CHWs conduct follow-up phone calls encouraging participants to mail the kits back (FIT, HPV). CHWs also call participants with the results of the home-based testing, and, if needed, do home visits for post-test counselling. All participants who elect to do home-based testing also receive a letter explaining their results which they can provide PCPs. All participants who elect to do home-based testing are still urged to follow-up with a PCP for routine primary care. CHWs explain to participants that the PCP can not only review the letter describing the tests the CHW provided to the participants but also assess for other additional screening tests or follow-up treatments the participants may need.

### Home-based screening tests

#### HIV screening: OraQuick HIV

Participants are screened for HIV 1(1/2) using oral swab testing: OraQuick® HIV (OraSure Technologies, Bethlehem, PA, USA). OraQuick Test detects HIV antibodies in the oral fluid. The test uses an oral swab to collect mucosal transudate by swabbing the gums. Participants can perform the test themselves or have the CHW (using appropriate blood-borne pathogen precautions) collect the swab for them. The CHWs received training and certification to meet the Florida Department of Health’s Minimum Standards for HIV Counselors. They were trained in OraQuick testing procedures as coordinated by a study co-investigator (SK) with extensive expertise in community-based HIV testing. Clients who test positive receive post-test counselling and are referred for free confirmatory testing at either one of the participating health centers of the South Florida AIDS network.

#### Hepatitis C screening: OraQuick HCV rapid antibody test

Participants are screened for HCV infection using a finger stick blood test, the OraQuick® HCV Rapid Antibody Test HCV (OraSure Technologies Inc., Bethlehem, PA, USA). This test has been shown to have a specificity of > 99.6%, which is nearly as specific as testing using venous blood. CHWs were trained on the procedures for HCV testing and post-test counseling by a co-investigator with extensive expertise in community-based HCV testing (ET). While patients can elect to do their own finger stick, in our prior HCV outreach programs, most participants have preferred for CHWs to do the finger stick. If a participant screens positive for HCV they will have the option of going to their PCP, a local FQHC, or the University of Miami’s Schiff Center for Liver Disease for confirmatory blood testing. For participants with positive confirmatory testing, the CHWs are available to explain and discuss in greater detail the serology results and the potential for complications for individuals living with HIV. The importance of screening for participants’ family members will also be emphasized. Participants are also advised that if their providers would like to place them on treatment, the CHWs can help find programs to cover the cost of the medication. For example, through a unique academic-industry partnership brokered by the University of Miami (UM)’s Schiff Center, the Center is able to provide free treatment for low-income, medically indigent patients who need HCV medications.

#### CRC screening: fecal immunochemical testing (FIT)

Participants are screened for CRC using home-based FIT testing. All CHWs are already experienced conducting community-based FIT screening from prior research studies and outreach initiatives [18]. CHWs have also been previously trained in FIT procedures including post-test counseling and the system to navigate patients for follow-up colonoscopy if needed. We use a Clinical Laboratory Improvement Amendments (CLIA)-approved FIT (OC-Auto Micro 80, Polymedco/Eiken, Cortlandt Manor, NY, USA). This FIT is a quantitative test with a cutoff for a positive, abnormal result of 100 ng hemoglobin/mL stool. Participants first receive education on the importance of CRC screening and how to properly perform the FIT test using educational materials from the American Cancer Society and the manufacturer. The study team translated these materials into Spanish and Haitian Creole using standard back-translation methods, and then tailored these materials to health literacy level of our study populations. Participants are provided with a FIT collection kit consisting of the collection device, instructions, and a mailer so that the sample may be sent to a central laboratory. CHWs subsequently make follow-up calls to reinforce education on proper collection and to ensure return of FIT specimens. Participant samples are mailed to a central UM laboratory using the mailers and self-addressed, stamped envelopes provided in the FIT kit. Individuals are asked to record the date of stool collection on the mailers, and the date of sample receipt by the laboratory will also be recorded. CHWs will deliver test results to participants by phone or in-person. If FIT results are normal, these patients will be instructed by the CHW they need to repeat CRC screening in 1 year. If the FIT test is positive, participants are advised that they need to undergo follow-up testing with colonoscopy. Participants can choose to follow-up with their own PCPs for colonoscopy, be referred to a local FQHC to arrange for such follow-up care, or have the CHWs assist with arranging follow-up. For example, the procedure can be done at the county’s local public hospital, Jackson Memorial Hospital. The CHWs are very familiar with navigating participants through the Jackson’s financial classification program for the medically indigent, so that they can get low-cost or free colonoscopies. The goal is to have the colonoscopy done within 90 days of the positive result. CHWs also provide education and participant reminders, ensuring proper preparation for colonoscopy and, if needed, helping arrange transportation to and from the colonoscopy appointment if necessary.

#### Cervical cancer screening: HPV self-sampling device

For home-based cervical cancer screening, CHWs will also continue using the same approach we have used in our prior studies [13, 14]. We use the Preventive Oncology International (POI)/National Institutes of Health (NIH) HPV self-sampling device. This device has been found to be of similar sensitivity to physician-collected specimens for high-risk HPV detection [19, 20]. The self-sampler includes a Dacron swab and a vial of ThinPrep. This self­sampler is similar in size to a regular tampon and very easy to use. The participant inserts the swab into her vagina until she meets resistance, which indicates the swab has reached her cervix. She then turns the swab three times to collect the sample, withdraws the swab, and then inserts the swab into the ThinPrep and stirs the swab 10 times. The CHWs refer those who screen positive to follow-up Pap smear and/or colposcopy at their local FQHC.

### Trial procedures 

#### Enrollment visit

During the enrollment visit, the CHE explains the study to the participants, answers participant questions, confirms participant eligibility, and obtains informed consent. Following informed consent, the CHE conducts an intake interview. Based on our experience with respondent fatigue as well as based on the recommendations of our community partners, we try to keep the intake interview to no more than 30 minutes in length. The interview includes questions on sociodemographic characteristics, previous experiences with disease screening for each of our four conditions, condition-specific disease knowledge, health beliefs and access to care. The intake interview (as well as informed consent and all other study measures), have been translated into Spanish and Haitian Creole by certified translators using validated back-translation methods.

#### Follow-up interview at 6 months

At 6 months, the CHW schedules each participant for a follow-up interview with a CHE who is blinded to study allocation. CHWs remind participants not to reveal their allocation to the CHE. Throughout the study, the CHEs (rather than the CHWs) conduct assessments to avoid bias. The follow-up interview includes some of the measures covered in the intake interview (screenings, health knowledge, access to care), as well as measures examining the acceptability of the intervention (for both study arms).

#### Participant timeline

The study is planned to be 60 months. Enrollment began in month 12 and will end by month 44. The recruitment goal is approximately 10 participants per month per community/study site. These targets and timelines are informed by our two previous trials within these communities (See Fig. 1).

**Fig. 1 Fig1:**
[figure not shown]
Schedule of enrollment, interventions, and assessments

### Outcome measures

#### Primary outcome

Our primary study outcome measure will be proportion of participants fully up to date on all their needed screenings for these four health conditions (three for men) at 6 months post-study enrollment. We will conduct intention-to-treat analysis based on study allocation. This outcome will be a binary (yes/no) variable. Participants in either group lost to follow-up at 6 months will be assumed not to have been screened in intention-to-treat analyses.

#### Secondary outcomes

As a secondary study outcome, we will examine each screening individually as a binary variable and look at the change in screening completion from baseline to 6-month follow-up in each arm of the study. For example, change in proportion of people up to date in screening for HCV in each arm. Another secondary outcome we will consider is the increase in median number of screenings done. For this endpoint, the possible ranges will be 0 to 4 for women (HIV, HCV, HPV, FIT) and 0 to 3 for men (HIV, HCV, FIT).

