### Sample size calculation

The baseline screening rates in our sample size calculation rates are obtained from our feasibility studies and local data. The overall sample size was chosen to ensure sufficient power to detect clinically meaningful effects associated with a 15% point increase in proportion of additional screening done in the home-based arm versus primary care arm using two-sided test for differences in proportion. Although we plan to conduct intention-to-treat analyses, in which all women lost to follow-up will be considered “unscreened,” we will also conduct analyses with lost to follow-up participants excluded. For these analyses, we need to account for attrition (21% in our previous study). In addition, in our subgroup analysis where we look at each individual test, we set alpha at 1.25% instead of 5% to account for multiple testing. Even with a 25% attrition rate, a proposed total sample size of 900 participants (450 per arm and 150 per site) will give us over 95% power for our primary outcome and 90% power for the subgroup analysis.

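### Read literally, scoring lost participants as unscreened understates each arm's change from baseline on the individual tests

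*Protocol article*

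**What the plan says.** Four provisions of the protocol article meet here.

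- **Handling of loss.** Under Primary outcome: "Participants in either group lost to follow-up at 6 months will be assumed not to have been screened in intention-to-treat analyses". Sample size calculation repeats the rule, referring to "intention-to-treat analyses, in which all women lost to follow-up will be considered “unscreened". That sentence speaks of women, but the Primary outcome section covers participants in either arm. The same paragraph adds that "we will also conduct analyses with lost to follow-up participants excluded".
- **Per-test endpoint.** Secondary outcomes treats each test as a binary variable and will "look at the change in screening completion from baseline to 6-month follow-up in each arm of the study". The example given is "change in proportion of people up to date in screening for HCV in each arm". No separate rule for lost participants appears there.
- **Count endpoint.** "Another secondary outcome we will consider is the increase in median number of screenings done", with a range of 0 to 4 for women and 0 to 3 for men.
- **Entry.** Under Inclusion criteria, participants must "report not having had appropriate screening for at least one of the following HIV, HCV, CRC, and cervical cancer". For two of the tests, overdue is defined as "never had a HIV test; never had a HCV test". For colorectal and cervical screening it depends on time since the last test.

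**The concern.** For the primary composite the rule is coherent. Nobody is fully up to date at entry, so scoring a lost participant as not fully up to date leaves baseline status unchanged and simply gives no credit for new screening.

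The per-test endpoints differ because the starting value need not be zero. Three participants, all lost at 6 months, show this:

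- Never tested for HIV at intake: no, then no. The change is 0, as a conservative rule intends.
- Tested for HIV years ago and enrolled because a stool test is due: yes for HIV at intake, then no. The change is −1, although a person who has been tested cannot become never tested.
- Colonoscopy 3 years before intake and enrolled for another test: yes for colorectal screening, then no. The change is −1, although the colonoscopy still counts under the 10-year criterion.

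In the last two cases the rule overwrites a status recorded at intake. At stake are the within-arm changes, which is how Secondary outcomes defines the per-test results. They would be too low by an amount that differs between tests, because baseline rates differ.

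**Working it through.** **Inputs from the protocol (Sample size calculation).** Attrition *a* is 21% (previous study) or 25% (planning value). There are 450 participants per arm, and the planned difference between arms is 15 points.

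**Assumed, because the protocol does not give them.** The baseline up-to-date rate *b* for a test is 20%, 40% or 60%. New uptake *p* among retained participants overdue for it is stated in each example. Loss is taken as unrelated to baseline status, and lapses among retained participants are ignored.

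**Step 1. The protocol's own figures.** No figure is given for these endpoints. The stated power does reproduce: with 450 × 0.75 ≈ 337 per arm and 42.5% versus 57.5% (the least favourable rates), power is 97.5% at two-sided 5% and 92.1% at 1.25%, against the stated over 95% and 90%. The present point does not rest on them.

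**Step 2. Change within one arm.**

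- Lost = unscreened: (1 − a)[b + (1 − b)p] − b
- Lost = no new screening: (1 − a)(1 − b)p
- Second minus first: b − (1 − a)b = **a × b**

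The gap does not depend on *p*. The literal rule shows a negative change when *p* is below ab / [(1 − a)(1 − b)].

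| Attrition | Baseline (assumed) | Understatement, points | Of 450 in an arm | Uptake below which change is negative |
|---|---|---|---|---|
| 21% | 20% | 4.2 | 18.9 | 6.6% |
| 21% | 40% | 8.4 | 37.8 | 17.7% |
| 21% | 60% | 12.6 | 56.7 | 39.9% |
| 25% | 20% | 5.0 | 22.5 | 8.3% |
| 25% | 40% | 10.0 | 45.0 | 22.2% |
| 25% | 60% | 15.0 | 67.5 | 50.0% |

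The counts of 450 apply to HIV, HCV and colorectal screening; cervical screening concerns women only.

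**Step 3. Two examples.**

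- a = 21%, b = 40%, p = 30%: literal rule 0.79 × (0.40 + 0.18) − 0.40 = +5.8 points; no new screening 0.79 × 0.60 × 0.30 = +14.2 points.
- a = 25%, b = 60%, p = 20%: literal rule 0.75 × (0.60 + 0.08) − 0.60 = −9.0 points; no new screening 0.75 × 0.40 × 0.20 = +6.0 points.

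**Step 4. Contrast between arms.** With equal attrition, a × b is the same in both arms and cancels. A true 15-point difference becomes 0.79 × 15 = 11.85 or 0.75 × 15 = 11.25 points under either rule, whatever *b* is. With a retention gap *g*, no treatment effect and p = 30%, the false difference is g[b + (1 − b)p] under the literal rule and g(1 − b)p under the other. For g = 5 points:

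- b = 20%: 0.05 × 0.44 = 2.2 versus 0.05 × 0.24 = 1.2 points, so 1.0 extra.
- b = 60%: 0.05 × 0.72 = 3.6 versus 0.05 × 0.12 = 0.6 points, so 3.0 extra.

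**Step 5. Median count.** In a simulation of 100,000 women (each test up to date with probability 50% at intake, those up to date on all four excluded, 15% uptake per overdue test), the mean count fell from 1.86 to 1.73 at 21% attrition and to 1.64 at 25% under the literal rule. It rose to 2.12 and 2.11 when intake status was kept. The median was 2 throughout.

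**The case against.** The strongest objection concerns scope. The rule stands under Primary outcome, where it does no harm, and is repeated only while explaining attrition. Being assumed not to have been screened can mean not screened during follow-up. The Abstract's outcome, completion within 6 months of enrolment, and the sample-size wording about additional screening both suit that meaning, under which the defect disappears. A statistical analysis plan may also settle it.

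This stands as a reason to call the text ambiguous. It does not clear it: both statements of the rule are worded for intention-to-treat analyses in general, the second uses a status word, and the HCV example under Secondary outcomes is a proportion up to date, which is also a status.

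Second, status can truly lapse. A stool test counts for 1 year and a Pap smear for 3. If test dates were spread evenly (an assumption), 6/12, or half, of the stool tests and 6/36, or about 17%, of the Pap smears would expire within 6 months. This stands: for those tests part of the recoding may be right, and the impossibility argument is confined to HIV and HCV.

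Third, the analysis excluding lost participants avoids the recoding altogether. It does, but it is a different analysis and leaves the intention-to-treat figures as they are.

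**Conclusion.** The point holds as a fault in how the rule, read literally, meets the per-test change endpoints. Each arm's change is understated by attrition times the baseline up-to-date rate. The direction follows for any attrition and baseline rate above zero when status cannot lapse, as for HIV and HCV. The size rests on baseline rates that the protocol does not give.

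A reader might infer more, and the document does not support it:

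- That the primary result is compromised. It is not, because everyone starts as not fully up to date.
- That a false fall of up to 15 points could swamp the planned 15-point effect. The planned effect is a difference between arms and the fall is within an arm. The term enters the contrast only through unequal attrition, of which the protocol gives no indication.
- That arms will show losses of screening. A negative sign needs low uptake together with a high baseline rate, and both are assumed here.
- That the median count is distorted. It may not move at all.

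The correction is worth making before analysis, since the Aims name the per-test increases as the secondary analysis and the sample-size section gives the individual tests their own alpha.

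**What to change.** State under Secondary outcomes that a participant lost at 6 months is taken to have had no new screening, and spell out what that means for each test:

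- **HIV and HCV:** keep the intake status of lost participants.
- **Colorectal and cervical screening:** either carry intake status forward unless the recorded test would have lapsed by 6 months, or analyse each test among those overdue for it at baseline, with lost counted as not screened.

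Keep the present rule for the primary composite and the analysis excluding lost participants as a sensitivity analysis.

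The cost is a few sentences and no new data collection, since the intake interview already covers previous screening for all four conditions. Single imputation remains. Some colorectal or Pap lapses may be misclassified if test dates are imprecise. Restricting to those overdue at baseline avoids the lapse problem but reduces the denominator to 450 × (1 − b) per arm, for example 270 at an assumed 40% baseline (before restricting to women for cervical screening), so power for those analyses would need restating.
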